## Abstract

**Background:**

A large proportion of apprentices shows addictive behaviours like cigarette smoking, alcohol, cannabis, or compulsive Internet use, others do not show such behaviours at all. *ready4life* is a smartphone application-based coaching program for apprentices, which takes into account the heterogeneity of adolescent addictive behaviour by promoting life skills and reducing risk behaviours. The main objective of the planned study is to test the efficacy of *ready4life* for addiction prevention among apprentices in Switzerland within a controlled trial.

**Methods/design:**

The efficacy of the *ready4life* coaching program will be tested in comparison to an assessment only control group, within a cluster-randomised controlled trial with one follow-up assessment after 6 months. At the beginning of the program, participants of the intervention group will receive an individual profile, showing areas in which they have sufficient resources and in which there is a need for coaching. Based on this feedback, they can select two out of the following six program modules: stress, social skills, Internet use, tobacco/e-cigarettes, cannabis, and alcohol. Participants of the intervention group will receive individualised coaching by a conversational agent (chatbot) for a period of four months. The coaching relies on motivational and social-cognitive principles of behaviour change. Within weekly dialogues, the coach provides individually tailored information in different formats, such as videoclips, texts, or pictures. Study participants will be 1318 apprentices with a minimum age of 15, recruited in approximately 100 vocational school classes in Switzerland. Primary outcome will be a composite measure for addictive behaviours including (1) at risk-drinking, (2) tobacco/e-cigarette smoking, (3) cannabis use, and (4) problematic Internet use.

**Discussion:**

The study will reveal whether this universally implementable but individually tailored intervention approach is effective in preventing the onset and escalation of addictive behaviors among apprentices.

**Trial registration:**

ISRCTN59908406 (registration date: 21/10/2020).

## Background

Adolescence is characterized by several biological, psychological and social changes, which have a significant impact on the further course of life [1, 2]. These changes enable greater autonomy, the building of social relationships as well as physical and social identity. However, they are also accompanied by an increased willingness to take risks during a time when the cognitive functions of the brain, e.g. to regulate emotions, are not yet fully developed [3]. This also increases the susceptibility to psychological and substance use disorders [4].

For adolescents starting an apprenticeship, entering work life is accompanied by additional changes and new challenges. Financial independence and social detachment from their parents result in a higher degree of autonomy. At the same time, the responsibility for one’s own actions increases and the workplace environment confronts them with the reality of work, which is often accompanied by stress, time and success pressure. Dealing with colleagues, superiors and business partners or customers also places new demands on the social competence of the apprentices. Accordingly, the beginning of the apprenticeship is associated with health risks, especially increased substance consumption. Although corresponding comparative figures from Switzerland are not available, the German drug affinity study shows a significantly higher proportion of tobacco smokers among apprentices than among high school students of the same age (36% vs. 19%), whereas the difference is less pronounced for binge drinking, an indicator of problematic alcohol consumption (43% vs. 39%) [5]. Apprentices, typically in the age of 15–18 years, represent a very heterogeneous group in terms of protective and risk behaviours, [6, 7] with a smaller proportion showing no substance use or addictive behaviours and another showing at least one or co-occurring at-risk behaviours. For example in vocational school students from Switzerland, 81% of smokers showed at-risk alcohol use whereas only 49% of non-smokers drink hazardously [7].

According to international reviews, general life-skills training programs that address social skills and simultaneously address social influences, e.g. by media or the peer group, are particularly suitable for preventing substance use or delaying the onset of addictive behaviours in younger adolescents and those who have not yet started using addictive substances [8]. In adolescents already using substances, interventions based on motivational and cognitive-behavioural principles proved to be effective in reducing addictive behaviours. They are effective at preventing the onset of specific substance use [9–11] or at decreasing problematic substance use [12]. Due to their age group and their heterogeneous risk profile ranging from none to several co-occurring addictive behaviors, both general life-skills training programs and motivational, cognitive-behavioral programs to reduce specific substances show potential.

Although schools provide access to large numbers of students, the implementation and dissemination of general life-skills or addiction prevention programs in schools pose serious challenges [13]. First, teachers and other professionals need the time, motivation, knowledge and skills to deliver the program. Second, extensive resources in terms of personnel, money, and time are required to administer such programs.

Digital intervention programs, e.g. delivered via computer, Internet or mobile phone have the potential to overcome the above-mentioned obstacles that hinder successful program implementation and larger-scale dissemination of preventive intervention programs in schools. They have a wide reach at a low cost and offer the opportunity to automatically deliver contents that can be accessed at any time and in any place [14, 15]. Furthermore, they allow an individual tailoring of the intervention program according to the individual health risks, resources and preferences. A meta-analysis on school-based eHealth interventions targeting multiple lifestyle risk behaviours [16] retrieved small and short-term intervention effects regarding diet, physical activity and screen time, but no effects for alcohol use or smoking behavior, however, no studies of mobile health (mHealth) intervention programs were included.

A promising means of delivering prevention programs is to do so remotely by mobile technologies. In Switzerland, as in most other developed countries, 99% adolescents between the ages of 12 and 19 own a mobile phone [17], rendering such programs universally implementable. Most adolescents use mobile phones on a daily basis for texting, taking pictures, playing games etc. Mobile phone-based interventions can provide almost constant support to users, in comparison to interventions that can only be accessed at specific times or locations. Mobile phone-based interventions also provide a discrete and confidential means of intervention delivery [18].

Although no mobile phone-delivered interventions addressing multiple lifestyle risk behaviours have been tested yet, mHealth interventions addressing single risk behaviours or general life-skills are promising [6, 19–21]. A controlled trial on a text messaging-based intervention to reduce problem drinking in vocational and upper secondary school students in Switzerland showed a significant intervention effect on the prevalence of binge drinking. For example binge drinking decreased by 6% in the intervention group and increased by 3% in the control group, relative to that of baseline assessment [19].

Another Swiss study showed the acceptance and potential effectiveness of a mobile phone-based life-skills training program for substance use prevention among non-smoking vocational school students [6]. Pre-post comparisons revealed a decrease in perceived stress and increases in several life skills addressed between baseline and the follow-up assessment. The proportion of adolescents with at-risk alcohol use significantly declined from 20% at baseline to 15% at follow-up.

Based on the promising effectiveness of mobile phone-delivered life-skills and addiction prevention programs among vocational school students and the heterogeneous addictive behaviour in this target group of late-adolescents, a reasonable next step is to test the efficacy of a program combining life-skills training and the prevention of multiple specific addictive behaviours within a controlled trial.

Within this study protocol, we describe a cluster randomised controlled trial testing the efficacy of a combined life-skills and addiction prevention coaching program delivered via smartphone to prevent addictive behaviours among apprentices recruited in vocational schools.

## Methods/design

### Design and hypotheses

We will conduct a two-arm cluster-randomised controlled trial to test the efficacy of *ready4life*, a smartphone-based life-skills and addiction prevention coaching program to prevent substance use among apprentices. We will test the efficacy of the intervention in comparison to an assessment only control group. The study participants will be assessed at baseline and at 6-months follow-up (Fig. 1). Our main hypothesis is that the individually tailored 4-month intervention program will be more effective than assessment only, in preventing the onset and escalation of addictive behaviours including (1) at risk-drinking, (2) tobacco/e-cigarette smoking, (3) cannabis use, and (4) problematic Internet use at 6-months follow-up.

**Fig. 1 Fig1:**
[figure not shown]
Study design

### Participants, setting and procedure

In most European countries, vocational schools are post-secondary public schools that are analogous to American community colleges. They are part of the dual educational system that combines apprenticeships in a business context and vocational training in a school context. Vocational schools provide general education and specific skills for each particular profession.

Based on data from the Swiss Federal Statistical Office, approximately half of all Swiss adolescents ages 16 to 19 currently attend vocational schools [22], with the highest proportions among adolescents ages 17 (males: 60%, females: 47%) and 18 (males: 57%, females: 45%). Vocational schools in the German speaking part of Switzerland will be invited to participate in the study by cooperating regional centres for addiction prevention.

Prevention specialists from these regional centres for addiction prevention will be trained and informed on the ready4life intervention program. These specialists will arrange sessions in the participating vocational school classes, lasting 30 min during regular school lessons reserved for health education. Within this session, the students will be informed about the program and invited to participate in a study testing innovative channels for the delivery of health-related information and life skills. The students will be informed about the study’s aims, design, assessments, reimbursement, and data protection. The chatbot coaching program, its friendly competition and the chance to win prizes will be described in detail, using a teaser video (https://www.r4l.swiss/). To ensure sufficient participation and thus representativeness of the sample [23], students will be informed that they would also receive a small reward for participating in the study (10 CHF for completing the follow-up assessment). Participating students will download the app on their smartphone and complete online study registration and baseline assessment. After giving informed consent, study participants will be invited to choose a username and provide their mobile phone number.

Subsequently, participants of intervention classes will receive an individual profile on their risks and resources and can select two topics (stress, social skills, Internet use, tobacco, cannabis, and alcohol) on which they will receive coaching, for a period of four months (two months per topic) by the chatbot. Participants of the assessment only control classes will not receive the intervention program. However, they will be invited to participate in the program after completion of the follow-up assessment in month 6. Follow-up assessment will be conducted in both study groups using a similar procedure: participants will be invited to complete the online follow-up assessments via SMS text messaging. Non-responders will additionally be addressed via computer-assisted telephone interviews conducted by research assistants.

### Ethical review

The study protocol was approved by the the Ethics Committee of the Faculty of Arts and Sciences at the University of Zurich (approval number 20.10.12; date of approval October, 16th, 2020). The trial will be executed in compliance with the Helsinki Declaration.

### Randomisation and allocation concealment

To avoid spill-over effects within school classes, we will conduct a cluster-randomised controlled trial using school class as a randomisation unit. Due to the heterogeneity of students in the different vocational schools, we will use a separate randomisation list for each school (stratified randomisation). Furthermore, to approximate equality of sample sizes in the study groups, we will use block randomisation with computer generated randomly permuted blocks of 4 cases [24].

The prevention specialists supervising the baseline assessment will be blinded to the group allocation of school classes. In addition, group allocation will not be revealed to participants until they had provided their informed consent, username, mobile phone number, and baseline data. Furthermore, the research assistants who perform the computer-assisted follow up assessments for primary and secondary outcomes will be blinded to the group allocation.

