### Data analyses

Generalized Linear Mixed Models will be used to test intervention effects for binary and count outcomes and Linear Mixed Models for continuous outcomes [38, 39]. These models account for both fixed and random effects and are particularly useful in analysing longitudinal and nested data (e.g., students within school classes). To test the efficacy of the intervention, we will test the variables “study group”, “time” and their interaction “study group x time” as predictors of the outcome criteria assessed at follow-up. If necessary, we will control baseline differences by adding additional baseline variables as covariates to the models. We will conduct both (1) intention to treat analyses and (2) complete case analyses considering all study participants with available follow-up data. For ITT analyses, we will use multiple imputation procedures as described elsewhere [40].

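### Randomisation is stratified by school, but the efficacy model names no school term; leaving school out may make the analysis somewhat conservative

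*Protocol article*

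**What the plan says.** In the protocol article, the section on randomisation and allocation concealment makes the class the unit ("using school class as a randomisation unit") and the school the stratum: "we will use a separate randomisation list for each school (stratified randomisation"). The reason given is prognostic: "Due to the heterogeneity of students in the different vocational schools". Within each school's list, allocation uses "computer generated randomly permuted blocks of 4 cases".

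The Data analyses section plans linear and generalised linear mixed models. On the terms it says: "we will test the variables “study group”, “time” and their interaction “study group x time” as predictors of the outcome criteria assessed at follow-up". The models are described as "particularly useful in analysing longitudinal and nested data (e.g., students within school classes"). Further terms enter under one rule: "If necessary, we will control baseline differences by adding additional baseline variables as covariates to the models".

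School is not named as a fixed effect, a random effect or a covariate. Nor does the text say that school is excluded, and it does not list the random effects in full.

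The sample size section uses a single class-level intra-cluster correlation (ICC) of 0.05 and takes no credit for stratification.

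**The concern.** Stratifying by a prognostic factor removes its variation from the true sampling error of the treatment comparison, because each school contributes classes to both arms. A model without school does not know this. It puts between-school differences into the class-level variance and treats them as noise. The estimate stays unbiased, but its standard error is then larger than the estimate's actual variability. Confidence intervals are too wide, the test rejects less often than its nominal 5% under the null, and some of the precision gained by the design is not used.

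The covariate rule is unlikely to repair this. It is triggered by baseline differences between arms, and school is the one factor that the randomisation is built to balance. The reason to adjust for a stratification factor is to get the variance right, not to correct an imbalance.

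At stake is efficiency in a trial that expects a small effect (d = 0.2).

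**Working it through.** **The plan's own figure.** A two-sample t-test at d = 0.2, two-sided α = 5% and 80% power, with Wilcoxon efficiency 3/π, needs 412 per group. The design effect is 1 + (13 − 1) × 0.05 = 1.60. Then 412 × 1.60 = 659.2, so 659 per group and 1318 in total, or 1318/13 ≈ 101 classes. All stated figures reproduce, and none depends on a school term.

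**Inputs for the check.** From the sample size section: 13 participants per class, ICC 0.05, 659 per group, d = 0.2. Assumed, because the article does not give it: the share *s* of the ICC that lies between schools. Also assumed: a continuous outcome, complete follow-up, and balance of arms within schools.

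**Follow-up comparison** (total variance set to 1)

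- Class-mean variance as a model without school sees it: 0.05 + 0.95/13 = 0.1231.
- Variance that actually drives the stratified comparison: 0.05(1 − s) + 0.95/13.
- SE ratio = √(first/second). True type I error = 2[1 − Φ(1.96 × ratio)].
- SE without school: √(2 × 1.60/(659 × 3/π)) = 0.0713. True SE: √(2 × 13 × second variance/(659 × 3/π)).
- Power without school: Φ((0.2 − 1.96 × 0.0713)/true SE). Power with school: Φ(0.2/true SE − 1.96).

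| Assumed share *s* | Second variance | SE ratio | True type I error | True SE | Power without school | Power with school |
|---|---|---|---|---|---|---|
| 25% | 0.1106 | 1.055 | 3.9% | 0.0676 | 81% | 84% |
| 50% | 0.0981 | 1.120 | 2.8% | 0.0637 | 83% | 88% |

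Over the whole possible range the SE ratio runs from 1.00 (s = 0) to 1.30 (s = 100%), and the true type I error from 5.0% to 1.1%.

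A simulation (100 classes of 13, permuted blocks of 4 within school, 20,000 runs) shows the same pattern. At s = 50% the SE without school was 1.089 times (5 schools) and 1.108 times (25 schools) the SE with school, with type I errors of 3.7% and 3.0%. These ratios are a little below 1.120, partly because the simulation also gave classes a class-by-time variance of 0.01.

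**Group-by-time contrast.** In a change from baseline, a stable school level cancels. The simulation, with an assumed within-person correlation of 0.5, compared the SE reported by a model without school with the true SE:

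- School shifts the level only (shares 0, 50% and 80%): ratio 0.995 to 1.006, type I error 4.9% to 5.1%. There is no inflation.
- School-by-time variance of 0.01 added (an assumption): SE about 4-6% too large, type I error 3.6% to 4.1%.

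The last result can be checked by hand. The class-mean change variance without a school part is 0.01 + 2 × 0.475/13 = 0.0831. Adding 0.01 for school-by-time gives 0.0931, and √(0.0931/0.0831) = 1.058.

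**The case against.** **The text does not exclude school.** Nesting is introduced only as an example ("nested data (e.g., students within school classes"), the random effects are not listed, and a journal article may leave the full model to an analysis plan that is not shown. This stands. A reader might infer that the model has no school term; the article supports only that it names none. But it does state its fixed terms and a rule for adding others, and that rule points away from a balanced stratifier, so the point concerns what is written as well as what is left unsaid.

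**The planned test is group by time, where stable school differences cancel.** This also stands, and it rules out saying that the standard error *is* too large. The reason given for stratifying concerns how students differ between schools, not how they change. However, the article ties its predictors to outcomes assessed at follow-up, states its hypothesis at 6 months, and powers a two-group Wilcoxon-Mann-Whitney comparison with no time term. A follow-up contrast is therefore a live reading.

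**The size is assumed.** True. The article gives neither a between-school variance nor a number of schools.

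**Nothing is invalid.** True. A reader might infer inflated type I error or an underpowered trial. The documents support neither: any error is conservative, and the sample size already carries the full ICC.

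**A school term is not free.** Partly right. Schools with few classes may have incomplete blocks. With fixed effects, a school whose classes all fall in one arm adds nothing to a between-arm follow-up comparison.

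**Conclusion.** The point holds as a gap between design and stated analysis: school is a stratification factor, it is not named in the efficacy model, and the covariate rule would tend not to bring it in. If it is omitted, inference may be conservative by an amount that the article does not allow one to compute.

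Under the assumed 25-50% share, a follow-up comparison would forgo about 3 to 5 percentage points of power (81% against 84%, and 83% against 88%). A group-by-time contrast loses little or nothing unless change over time differs by school.

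Power without school stays at or above the planned 80%, given full follow-up. The calculations treat the outcome as continuous. The primary outcome is a 0-4 count, so a generalised linear mixed model would follow the same pattern only approximately.

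**What to change.** State in advance that school enters every efficacy model alongside the class random intercept. A random intercept for school above class is the safer default; a fixed effect is suitable if each school contributes several classes in both arms. Include school in the multiple imputation model as well, so that the imputed data respect the same structure.

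The information is already held, since the randomisation lists are kept by school. The change is a sentence in the plan and one term in each model. The cost is some degrees of freedom, plus lost information from single-arm schools if fixed effects are used with many small schools. Prespecifying the term also avoids deciding about school after the data are seen.

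### A single published block size of 4 within each school's list weakens allocation concealment towards the prevention specialists if a school's classes are enrolled in sequence

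*Protocol article*

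**What the plan says.** All passages are in the protocol article.

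- *Randomisation and allocation concealment*: the trial is randomised "using school class as a randomisation unit", with one list per school. Blocking is used "to approximate equality of sample sizes in the study groups", by "computer generated randomly permuted blocks of 4 cases". Since the unit is the class, a case here must mean a class. Only one block size is named.
- Same section, on blinding: "The prevention specialists supervising the baseline assessment will be blinded to the group allocation of school classes". For students, "group allocation will not be revealed to participants until they had provided their informed consent, username, mobile phone number, and baseline data".
- *Participants, setting and procedure*: "These specialists will arrange sessions in the participating vocational school classes, lasting 30 min during regular school lessons". In these sessions students hear about the study and the coaching, are invited, download the app, consent and complete baseline. After that, "participants of intervention classes will receive an individual profile on their risks and resources" and choose two topics. Control classes get neither.
- *Sample size calculation*: about 100 classes, 13 participants per class on average, expected effect d = 0.2. The number of schools and of classes per school is not given.

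**The concern.** The stated blinding covers the class in front of the specialist up to the end of baseline. It does not obviously cover the next class in the same school. Once a class has finished, its arm shows on the students' phones, in a session that the specialist supervises. With one list per school and a fixed small block, the arms of finished classes carry information about the arms still to come.

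This matters because students consent one by one, after a presentation by the person who might be able to predict the arm. How warmly the programme is presented can affect who joins, and differently by arm. That is recruitment bias in a cluster trial. The *Data analyses* section would add baseline covariates where necessary, which corrects only for measured differences. With an expected effect of d = 0.2, modest selection could count. The concern does not depend on whether the class has formally been allocated before consent: a predictable next list position is enough.

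**Working it through.** **The plan's own figures.** The article gives no figure on predictability. Its sample size reproduces: 393 per group for d = 0.2, divided by the Wilcoxon efficiency 3/π, gives 411.5, hence 412; design effect 1 + (13 − 1) × 0.05 = 1.60; 412 × 1.60 = 659.2; and 1318 / 13 = 101.4 classes. Predictability does not alter these numbers.

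**One block of 4.** Inputs from the article: block size 4, one list per school, 1:1 (implied by 659 per group). Assumed, because not stated: the guesser knows the block size, the list order and all earlier arms in that school, and classes are enrolled in list order. There are 6 equally likely sequences of two A and two B.

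- Class 1: never certain; best guess right 1/2.
- Class 2: never certain; best guess right 2/3 (two of the three remaining places belong to the other arm).
- Class 3: certain if the first two share an arm, in 2 of 6 sequences = 1/3; best guess right 1/3 × 1 + 2/3 × 1/2 = 2/3.
- Class 4: always certain.

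Certain share in a complete block: (0 + 0 + 1/3 + 1) / 4 = 33.3%. Best-guess success: (0.500 + 0.667 + 0.667 + 1) / 4 = 70.8%.

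**By number of classes per school (assumed).** The last block in a school may be incomplete, so the share varies:

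| Classes per school | Certain | Best guess right | Certain, of 100 classes | Participants (× 13) |
|---|---|---|---|---|
| 1 | 0% | 50.0% | 0 | 0 |
| 2 | 0% | 58.3% | 0 | 0 |
| 3 | (1/3)/3 = 11.1% | 61.1% | 11.1 | 144 |
| 4 | (4/3)/4 = 33.3% | 70.8% | 33.3 | 433 |
| 6 | (4/3)/6 = 22.2% | 66.7% | 22.2 | 289 |
| 8 | (8/3)/8 = 33.3% | 70.8% | 33.3 | 433 |

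**If the list order is unknown but an even split is expected.** With m classes per arm seen in random order, the expected length of the final run, all of which is forced, is 2m/(m + 1). Four classes (m = 2): 4/3 of 4 = 33.3%, unchanged. Eight classes (m = 4): 8/5 = 1.6 of 8 = 20%.

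**After the change.** Eight classes per school, enrolled in list order; the guesser knows the set of sizes but not the current size (simulation, 4,000 runs per setting for the varying sizes):

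| Block sizes | Certain | Best guess right |
|---|---|---|
| Fixed 4 | 33.3% | 70.8% |
| 2, 4 | 9.4% | 71.4% |
| 4, 6 | 5.9% | 66.7% |
| 2, 4, 6 | 2.8% | 68.5% |

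Varying sizes remove most of the certainty and little of the better-than-chance guessing.

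**Cost in balance.** With 8 classes and sizes 4 and 6 drawn equally often, the split is not 4:4 when the last block is cut short unevenly. A first block of 4 followed by four places of a 6-block is uneven with probability 1 − 9/15 = 0.40. A first block of 6 followed by two places is uneven with probability 1/3 (4-block) or 0.40 (6-block). In total, 1/2 × 1/2 × 0.40 + 1/2 × (1/2 × 1/3 + 1/2 × 0.40) = 0.283. An uneven split is 5:3, so the expected difference is 2 × 0.283 = 0.57 of a class, against 0 with fixed blocks of 4.

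**The case against.** The strongest reply is that the article states none of the conditions for prediction. It does not say that specialists know the block size or list order, that one specialist handles successive classes of a school, that specialists learn each finished class's arm, or that classes are randomised one by one. Registration, baseline and feedback run on the students' own phones, and revelation is described towards students only. Printing a block size in a journal does not mean the regional centres were told it. List custody and timing are also details that an article may leave to the full protocol. A teaser video limits how far the presentation can vary, and control students are offered the programme after follow-up.

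Much of this stands. A reader might infer that the specialists' blinding is defeated, or that 33 classes and 430 participants is the expected damage. The documents support neither: the first needs knowledge that they do not attribute to the specialists, and the second is the top of a range that starts at zero.

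Two parts do not dispose of the point. Unknown list order does not help in a school with four classes, where an expected even split is enough. Randomising a school's classes all at once protects the choice of classes, but not student recruitment, if sessions fall at different times and profiles appear after each one. And the block size is a choice that the article states, not a detail it omits.

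**Conclusion.** The point holds as a conditional weakness. One small, fixed and published block size per school makes later arms partly predictable to a specialist who learns the arms of earlier classes, and the article describes no safeguard against that learning. Under worst-case knowledge, between 0 and about 33 of about 100 classes (0 to about 430 participants) have a certain allocation in advance, depending on the unstated number of classes per school; best-guess success is at most 71% against 50%. The first two classes of a block are never certain, and schools with one or two classes give no certain allocation. The size and direction of any resulting bias cannot be derived from the article. The withholding of allocation from students until after baseline, the blinding of the telephone assessors and the sample size are not affected. The change is worth making because it is cheap.

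**What to change.** In *Randomisation and allocation concealment*:

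1. Replace the single block size with randomly varying block sizes of classes (for example 4 and 6, or 2, 4 and 6), and write classes instead of cases.
2. State that the lists are generated centrally, say who holds them, and do not disclose the sizes to the regional centres.
3. Register all of a school's classes before its list is applied, and assign them to list positions in random order.

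The cost is a changed list-generation script, a few sentences of text, the need to know a school's classes beforehand, and an expected difference of about half a class between arms within a school of eight.

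Only where a school's sessions fall close together, profiles could optionally be released after its last class has completed baseline. This removes the source of the information, and so also the residual guessing that varying blocks leave. It has a real delivery cost: it changes how the app releases content and puts a gap between baseline and the start of a four-month programme assessed at six months.
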